**FIGURE 1 F1:**
[figure not shown]
Study design flow diagram.

The inclusion/exclusion criteria for this study are as follows:

Inclusion Criteria:

1.At least age 182.Be able to remain in the session for 3-4 h3.Be able to perform scripted tasks4.Be able to provide informed consent5.Be able to wear the wearable devices at all times during the study6.Have completed a COVID-19 vaccine regimen and can provide written documentation verifying vaccination status at least (14) days prior to the commencement of the research study.

Exclusion criteria:

1.Any reported mood, anxiety, or major health disorders2.Current use of steroid-based medications3.History of drug/alcohol abuse4.Recovering from nicotine dependency and cannot use a nicotine patch for two hours prior to and throughout the study5.Consumption of excessive amounts of caffeine (more than 400 mg per day as defined by the FDA (Food and Drug Administration, 2018)6.Severe sleep disturbance based on participants’ self-report (e.g., Sleep apnea)7.Pregnancy8.History of cognitive impairment9.Not completed COVID-19 vaccine regimen10.Cosmetics or head products that might interfere with the electroencephalography (EEG) recordings.

Eligible participants will be asked to refrain from caffeine two hours before the start of the study due to its effect on the physiological measures of interest. Participants recovering from nicotine dependency will need to use a nicotine patch up to two hours before the study. All consented participants will be screened for symptoms of COVID-19 prior to coming into the lab. Participants and study staff will be required to wear a mask throughout the experiment session. The study protocol has been reviewed and approved by Mayo Clinic Internal Review Board (21-005885).

### MindBreaks Relaxation Room

A MindBreaks relaxation room will be used for this study to determine how the auditory and visual stimuli of the room affect physiological measures, cognitive performance, and self-report of stress during the recovery epoch of the Trier Social Stress Test (see section “Trier Social Stress Test Protocol”). The MindBreaks room is designed to deliver short, effective, and restorative breaks to help increase energy, reduce stress, enhance mood, improve focus, and boost performance (MindBreaks, 2022). The room contains biophilic visual stimuli in the form of an artificial green wall and plants, calming lighting, and a virtual nature skylight to promote relaxation and reduce stress (Berto, 2014; An et al., 2016; Wooller et al., 2018; Hedblom et al., 2019). Immersive natural auditory stimuli from the MindBreaks audio library are played in the room through Sonos^®^ speakers (*Sonos Inc., California, United States*) to provide a calming and relaxing experience (Alvarsson et al., 2010; Largo-Wight et al., 2016; Wooller et al., 2018). For this study, participants will experience the auditory and visual stimuli, auditory stimuli only, visual stimuli only, or no stimuli (control condition), depending on the cohort. Participants who do not experience the biophilic visual stimuli will see neutral curtains covering the walls of the room.

### Trier Social Stress Test Protocol

Participants will perform the Trier Social Stress Test (TSST) to induce an experimentally controlled acutely stressful event (Kirschbaum et al., 1993). The TSST is a widely used laboratory procedure that places participants in a socially evaluative situation that reliably induces mental stress and elicits measurable physiological stress responses (Birkett, 2011). The experimental session is divided into three different epochs: (1) baseline (waiting period upon arrival), (2) stress induction task, and (3) recovery. During the baseline epoch, participants will rest for 30 minutes in the control condition (no biophilic visual or auditory features) to stabilize physiological responses and acquire baseline stress levels. During the stress induction task, participants will perform the TSST which consists of three 5-min phases: (1) the preparation phase, (2) the presentation phase, and (3) the mental arithmetic phase. During the preparation phase, the participant is asked to imagine they have applied for their dream job and given writing materials to make notes about what makes them the ideal candidate. During the presentation phase, the participant will argue why they are the best candidate for the job in front of an interview panel and while being recorded with a video camera and microphone. During the mental arithmetic phase, participants are asked to count backward by 13 starting from 1,022. During the recovery epoch, participants will rest in the MindBreaks room for 40 min while experiencing one of four conditions: auditory-visual stimuli, auditory stimuli, visual stimuli, or control condition (no stimuli). Previous studies have used different durations for each of these epochs (Narvaez Linares et al., 2020). Here, we will adjust the baseline and recovery epoch durations based on how quickly physiological signals and cognitive performance recover during the study optimization period involving 20 participants. Figure 2 depicts a timeline of the different epochs of the TSST, including the times when participants will be asked to perform the cognitive assessment tasks and fill out stress and anxiety self-reports.

**FIGURE 2 F2:**
[figure not shown]
A timeline of the different epochs of the TSST. Dashed lines indicate time points in the experiment when stress-related surveys are administered (indicated by a △) and/or when working memory assessments (SSPAN, OSPAN) are administered (indicated by a *). Wearable devices are recorded continuously from the start of the Baseline epoch to the end of the Recovery 2 epoch. Measures are aligned around the start of the Stress Induction Task (*T* + *0min*).

### Physiological Measures of Stress

There are numerous physiological responses to stress that can be detected through cardiac and neural measurements (Taelman et al., 2009; Brouwer et al., 2011; Jebelli et al., 2018; Arsalan et al., 2019; Bahadorani et al., 2021). The use and availability of wearable devices for recording such physiological measurements have increased substantially over the last decade (Can et al., 2019). In this study, we propose using multiple wearables to record measures of heart rate (HR), heart rate variability (HRV), and neural activity *via* electroencephalography (EEG). Table 1 describes the different specifications of each of the wearable devices being used in this study.

**TABLE 1 T1:** Features of the wearable devices to acquire physiological signals during a study session.

Device	Sampling rate	Sensor type	Variable measured	On-body location	Data collection application
Apple Watch Series 6	Variable, approximately once every 5-6 s using Workout App	Optical	HR	Wrist non-dominant hand	Apple Health
Empatica E4	1 Hz	Optical	HR	Wrist dominant hand	Empatica E4 Manager
Polar Verity Sense	1 Hz	Optical	HR	Upper arm non-dominant hand	Polar Flow
Polar H10	1 Hz	ECG	HRV	Chest	Elite HRV
Dreem 3	250 Hz	EEG	EEG	Head	Alfin

**Note: HR – Heart Rate, HRV – Heart Rate Variability, ECG – Electrocardiogram, EEG – Electroencephalogram.*

#### Cardiac Measures (Heart Rate, Heart Rate Variability)

Heart rate, the number of times the heart beats per minute, will be measured at the following parts of the body: 1) the wrist on the non-dominant hand using an Apple Watch Series 6 (*Apple Inc., California, United States*); 2) the wrist on the dominant hand using an Empatica E4 (*Empatica Inc., Massachusetts, United States*); 3) the upper arm on the non-dominant hand using a Polar Verity Sense (*Polar Electro, United States*); and 4) the chest using a Polar H10 (*Polar Electro, United States*) heart rate monitor. The validity and reliability of HR measurements from Apple Watch Series 6 (Hajj-Boutros et al., 2021), Empatica E4 (Menghini et al., 2019), and Polar Verity Sense (Kim et al., 2021) have been evaluated and are suitable for this research study. Each of these wearable devices will be placed on the participant based on each manufacturers’ guidelines. The Empatica E4 stores data locally on the device, whereas the other devices are paired to an Apple iPhone 11 to record data through the respective applications listed in Table 1.

Heart Rate Variability (HRV), a measure of the variation in time between each heartbeat, is also an important measurement of recovery from stress (Castaldo et al., 2015, 2016; Ghiasi et al., 2020). Here, the Polar H10 (*Polar Electro, United States*) will be used to collect R-R intervals using the Elite HRV app throughout the experimental session and Kubios HRV Premium software (version 3.3.1) will be used to retrieve HRV time- and frequency-domain indices (Lipponen and Tarvainen, 2019). The accuracy of R-R intervals (RR) capturing from Polar H10 is comparable to a reference grade device and suitable for obtaining reliable HRV-related metrics (Umair et al., 2021). Average HR and HRV measurements such as the mean of R-R intervals (Mean RR), a standard deviation of a normal R-peaks (NN) (SDNN), the square root of mean squared difference between normal heartbeats (RMSSD), the percentage of adjacent NN intervals that differ from each other by more than 50 ms (pNN50), very-low-frequency (0.0033 - 0.04 Hz, VLF), low-frequency (0.04 – 0.15 Hz, LF), and high-frequency bands (0.15 – 0.40 Hz, HF) will be collected and analyzed for each epoch of the experiment.

Our selection of HRV metrics is based on a meta-analysis examining HRV in acute mental stress done by Castaldo et al. (2015). Given that time-domain HRV metrics, Mean RR, SDNN, RMSSD, and pNN50 have been shown to be affected by acute stress (Castaldo et al., 2015), we will compare these metrics before, during, after stress to determine when it recovers to baseline levels. Similarly for the frequency domain, HF has been shown to decrease during stress (Castaldo et al., 2015; Shaffer and Ginsberg, 2017), so we will compare the HF of HRV metrics before, during, and after stress to determine when HF power increases back to baseline levels. As exploratory, *post hoc* analyses, we will also look at VLF of HRV to determine if there are any task-related changes after stress. Usui and Nishida (2017) has shown that VLF slowly recovered after a mental task compared to HF, thus it would be worth to examine whether existence of sensory features could promote the recovery process of VLF.

#### Neural Activity

Electroencephalography (EEG) is a well-established, non-invasive approach to measuring neural activity. In this study, the Dreem headband (*Dreem, Paris, France*) will be used to determine how neural activity changes (1) before and after the stress induction task, and (2) when recovering from stress based on the different biophilic features of the recovery room. The Dreem headband has been used to classify sleep stage through EEG and its accuracy is comparable with polysomnography (Arnal et al., 2020; Pépin et al., 2021). Although we are not using the device to study sleep, the neural recordings are expected to be similar in quality during the baseline and the recovery epochs of the study. Additionally, the Dreem headband is a dry electrode system designed for comfort which will be advantageous for the prolonged use during this study. The Dreem 3 headband has 5 electrodes located at O1, O2, F7, F8, and FP2 based on the standard 10-20 orientation (note, FP2 is used as a reference signal). Signals are sampled at 250 Hz and will be recorded using the Alfin app provided by Dreem. To account for the lateralized reference electrode (FP2), we will apply a common average reference to attempt to account for any lateralized effects. EEG signals will be preprocessed to remove artifact noise using independent components analysis. If EEG signals during the speech and mental arithmetic phases are too noisy to analyze, only the preparation phase of the TSST will be included for subsequent analysis.

Electroencephalography analyses will be conducted mainly in python using the MNE toolbox (Gramfort et al., 2013). As the primary outcome, we will compare alpha spectral power (8-13Hz) before, during, and after the stress epoch, as this has been shown to significantly decrease in response to a stressor (Vanhollebeke et al., 2022). As exploratory analyses, we will compare spectral power before, during, and after the stress epoch in the theta (4-8Hz), beta (13-32Hz), and gamma/high-gamma (32-100Hz) frequency bands similar to Arsalan and colleagues (Arsalan et al., 2019), as well as frontal alpha asymmetry similar to prior studies (Quaedflieg et al., 2015; Ehrhardt et al., 2021; Hu et al., 2021). The lateralized reference in the Dreem headband (FP2) will be taken into consideration when interpreting any frontal alpha asymmetry results, as this could produce false positive results. Although these exploratory analyses were not shown to have significant responses to a stressor based on the meta-analysis conducted by Vanhollebeke and colleagues (Vanhollebeke et al., 2022), the focus here will be on whether neural activity in these frequency bands significantly modulates in response to the stressor and the specific sensory stimuli during the recovery epochs, which to our knowledge has not been previously examined.

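### Alpha-power differences between cohorts with and without the visual scene mix a direct response to the scene with recovery from stress, so they should not be read as recovery alone

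*Protocol article*

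**What the plan says.** All references are to the protocol article.

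- **Outcome.** Neural Activity: "As the primary outcome, we will compare alpha spectral power (8-13Hz) before, during, and after the stress epoch". The reason given is "as this has been shown to significantly decrease in response to a stressor". The other frequency bands and frontal asymmetry are labelled exploratory.
- **Use across cohorts.** The same section says the headband will show how neural activity changes around the stress task and also "when recovering from stress based on the different biophilic features of the recovery room". The Introduction hypothesises a faster return to pre-stress levels with both stimuli than with one or none.
- **Baseline.** Trier Social Stress Test Protocol: "participants will rest for 30 minutes in the control condition (no biophilic visual or auditory features".
- **Recovery.** Same section: "participants will rest in the MindBreaks room for 40 min while experiencing one of four conditions". MindBreaks Relaxation Room describes "biophilic visual stimuli in the form of an artificial green wall and plants, calming lighting, and a virtual nature skylight", and for the other cohorts: "Participants who do not experience the biophilic visual stimuli will see neutral curtains covering the walls of the room".
- **Sensors.** "The Dreem 3 headband has 5 electrodes located at O1, O2, F7, F8, and FP2", with FP2 as the reference.
- **The article's own remark.** In introducing mobile EEG, the Introduction cites its use to study changes in neural activity with stress and with sensory stimulation.

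**The concern.** Alpha is justified as a stress marker: it falls under stress, and its return is read as recovery. That reading needs the assigned room condition to act on alpha only through stress. For the visual factor, the assigned condition also changes what participants are looking at while alpha is recorded. If the scene itself changes alpha, a cohort could seem to recover faster or slower with no difference in stress.

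The visual scene is one of the two room features under test. The article warns that the FP2 reference could produce false positives for frontal asymmetry, but gives no similar caution about visual input and alpha power.

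**Working it through.** **1. Visual scene by epoch.** The control condition is the one without stimuli, and cohorts without visual stimuli see curtains. This gives:

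| Cohort | Baseline | Recovery |
|---|---|---|
| Auditory-visual (AV) | control | biophilic scene |
| Visual (V) | control | biophilic scene |
| Auditory (A) | control | curtains |
| Control (C) | control | curtains |

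The scene changes between baseline and recovery only in AV and V. The Figure 2 caption says the wearables record continuously, so recovery EEG is taken while the stimuli are present.

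**2. What each contrast estimates.** Write the alpha change from baseline to recovery in cohort j as R_j + D × (1 if the scene is present, 0 if not). R_j is the change due to recovery from stress, and D is the direct response to the scene relative to curtains.

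- AV − C = (R_AV − R_C) + D
- AV − A = (R_AV − R_A) + D
- V − C = (R_V − R_C) + D
- V − A = (R_V − R_A) + D
- AV − V = R_AV − R_V
- A − C = R_A − R_C

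D stays in 4 of the 6 pairwise contrasts and cancels in 2 (for AV − V, if sound does not alter D). Of the three comparisons in the Introduction's hypothesis (AV against A, V and C), two contain D. Subtracting baseline does not remove D, because no baseline contains the scene. Randomisation does not remove it either, because D follows from the assigned condition.

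**3. The plan's own figure.** The article gives no planning figure for alpha. Its sample size (Power Analyses) rests on the cognitive measures: 18 per group for 80% power at a 1 SD difference and a 0.05 level, raised to 20. Taking a two-sided test of a single measure, n = 2 × (1.960 + 0.842)² = 15.7, so 16 per group. The exact t-test needs 17, and at 18 its power is 83.0%. The stated 18 is thus reproduced to within 2, and the present point does not depend on it.

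**4. Illustration of size.** Assume no difference in recovery (all R_j equal) and a direct response of d SD of the analysed alpha measure. The values of d are assumptions. The chance of a significant two-sided 5% t-test, with noncentrality d × √(n/2), is:

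| d | 20 vs 20 | 40 vs 40 (visual factor pooled) |
|---|---|---|
| 0 | 5% | 5% |
| 0.25 | 12% | 20% |
| 0.5 | 34% | 60% |
| 0.75 | 64% | 91% |
| 1.0 | 87% | 99% |

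The test is symmetric, so a negative d gives the same chances with the sign reversed. The error could favour the visual cohorts or count against them.

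**The case against.** Several counter-arguments have force.

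- **Primary.** The word is set against the exploratory EEG analyses, and the quoted sentence compares epochs, not cohorts. A reader might infer that the trial's single primary endpoint is compromised. The objective covers physiology, cognition and perceived stress, and the trial was sized on cognition, so that is not supported. The cohort comparison of EEG is still stated, in Neural Activity and in the hypothesis.
- **Eye state.** A reader might infer that the cohorts differ in whether their eyes are open. No cohort is assigned a different eye state. The article is silent, and such an instruction may sit in the full protocol, so its absence is not a finding. The point does not need it: an eyes-open rule leaves the scene difference, and eyes closed throughout would remove the visual intervention.
- **Direction.** A reader might infer that the scene lowers alpha and so biases against the auditory-visual hypothesis. That rests on general physiology and assumed rates of eye closure. The documents do not give a direction.
- **Frontal channels.** A reader might infer that common average referencing spreads occipital alpha equally to F7 and F8. For a fully coherent source at O1 and O2 only, averaging four channels gives 0.5 at the occipital sites and −0.5 at the frontal ones. With FP2 included it gives 0.6 and −0.4, so frontal power is 0.16/0.36 = 44% of occipital. The article does not say which channels enter the average.
- **Separability.** It would be too strong to say that no analysis can separate the two effects. The span tasks are done on a desk-placed iPad at set times (Cognitive Assessments, Figure 2). The Discussion plans to examine physiology during the task at baseline and at the end of recovery. These windows share a visual target. The separation is partial, because surroundings and task load remain.
- **Speed of recovery.** A constant offset would not bias the slope within recovery. It would bias the time to return to pre-stress levels, which is how the hypothesis is worded.

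**Conclusion.** The point holds for alpha across the visual factor. Recorded during free rest, a visual-versus-no-visual alpha difference is the sum of a direct response to the scene and any difference in recovery, and the article describes no planned step to separate them. The size and direction of the direct response cannot be known from the documents. The percentages above show only what assumed values would imply, and the error is nil if the scene has no direct effect.

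The point does not reach the trial as a whole. Auditory versus control and auditory-visual versus visual are unaffected by the scene difference, and heart rate, heart rate variability and self-report can still speak to the visual feature. The Introduction's remark covers sensory stimuli in general, so a direct response to sound is not excluded in the two equal-scene contrasts. The claim made here concerns only the scene. This is a low-cost improvement that changes what may be concluded from alpha, not a fault that invalidates the design.

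**What to change.** 1. State that the alpha recovery claim is limited to contrasts with equal visual input (auditory versus control; auditory-visual versus visual). State also that a visual-versus-no-visual alpha difference during free rest will not be read as recovery. The visual feature is then judged on heart rate, heart rate variability and self-report. The cost is a change of wording, and alpha says less about the visual feature.
2. If alpha is to inform the visual feature, take it from windows with a common visual condition, in one of two ways:
   - Use the existing iPad-task windows at baseline and in recovery. This needs no new data collection but is only a partial control, for the reasons given above.
   - Add short fixed windows under the same visual condition in all cohorts, at baseline and in recovery. The headband is already worn, so the burden is small. The room exposure is briefly interrupted, and the pauses may themselves be restful and dilute cohort differences.

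The choice should be made before the main-trial data are collected, because recordings taken only during free rest under different scenes cannot be put under a common visual condition afterwards.

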### Cognitive Assessments

Participants will perform cognitive assessments to assess working memory function at specific times during the stress induction task. Acute stress has been shown to affect performance on working memory tasks (Vedhara et al., 2000; Shields et al., 2016; Jiang and Rau, 2017). In this study, participants will use a cognitive assessment application designed by the Well Living Lab (Jamrozik et al., 2019; Aristizabal et al., 2021a) to perform two working memory tasks: the Operation Span (OSPAN) task and the Symmetry Span (SSPAN) task (Foster et al., 2015; Draheim et al., 2018). Participants will perform these assessments on a 12.9” iPad Pro (*Apple Inc., California, United States*) located on a desk to ensure consistent placement across participants. Although some studies have required 85% accuracy on the processing components of the task (math accuracy for OSPAN, symmetry accuracy for SSPAN), other studies have found similar task performance measures without requiring such a processing accuracy threshold (Đokić et al., 2018). To ensure we have cognitive measures for each time step in the TSST (outlined in Figure 2), we will not require a processing accuracy threshold when analyzing changes in cognitive performance.

Two dependent measures will be used for analysis of both SPAN tasks: Unit Score and Load Score. The Unit Score is the average of the proportion of letters or grids participants can recall correctly in the appropriate order in each set. The Load Score is calculated from the sum of correctly recalled elements from all trials, regardless of the order. Both scores will be used to assess changes in working memory capacity before and after the stress induction task.

